## Abstract

**Background:**

Timely access in primary health care is one of the key issues facing health systems. Among many interventions developed around the world, advanced access is the most highly recommended intervention designed specifically to improve timely access in primary care settings. Based on greater accessibility linked with patients’ relational continuity and informational continuity with a primary care professional or team, this organizational model aims to ensure that patients obtain access to healthcare services at a time and date convenient for them when needed regardless of urgency of demand. Its implementation requires a major organizational change based on reorganizing the practices of all the administrative staff and health professionals. In recent years, advanced access has largely been implemented in primary care organizations. However, despite its wide dissemination, we observe considerable variation in the implementation of the five guiding principles of this model across organizations, as well as among professionals working within the same organization.

The main objective of this study is to assess the variation in the implementation of the five guiding principles of advanced access in teaching primary healthcare clinics across Quebec and to better understand the influence of the contextual factors on this variation and on outcomes.

**Methods:**

This study will be based on an explanatory sequential design that includes 1) a quantitative survey conducted in 47 teaching primary healthcare clinics, and 2) a multiple case study using mixed data, contrasted cases (*n* = 4), representing various implementation profiles and geographical contexts*.* For each case, semi-structured interviews and focus group will be conducted with professionals and patients. Impact analyses will also be conducted in the four selected clinics using data retrieved from the electronic medical records.

**Discussion:**

This study is important in social and political context marked by accessibility issues to primary care services. This research is highly relevant in a context of massive media coverage on timely access to primary healthcare and a large-scale implementation of advanced access across Quebec. This study will likely generate useful lessons and support evidence-based practices to refine and adapt the advanced access model to ensure successful implementation in various clinical contexts facing different challenges.

## Background

### Importance and impact of the research

Accessibility is one of the major concerns facing health systems worldwide [1]. Having access to health services is a high priority for the population, clinicians and decision-makers alike [2]. Timely access, such that patients are able to access care when they need medical attention, often referred as same or next day appointment is one of the 10 pillars of the *Patient-centered Medical Home* [3]. Among many interventions developed around the world to improve timely access, advanced access figures as one of the most highly recommended model to reduce wait times in primary care settings [4–6]. Originally developed in the United States, advanced access has been adopted in many countries and is considered a cornerstone of primary care services of high quality and performance. Based on greater accessibility linked with patients’ relational and informational continuity with a primary care professional or team [7], this organizational model is based on five guiding principles (see Fig. 1) [8]: 1) Balancing supply (appointments available) and demand (requests for appointments) consists of assessing the need for services by weighting the patients’ needs according to their medical conditions and their age and adjusting the supply of services accordingly. 2) Reducing the negative backlog by eliminating the wait list and setting up a communication strategy using a range of tools (e.g. letters, telephone welcome message, notice in the local newspaper) to inform and educate patients about the new model. 3) Reviewing the appointment scheduling system consists of planning physicians’ schedules over a short term (two to three weeks) to be able to anticipate demand for consultations and to permanently offer appointment slots (e.g. same-or next day) for acute and urgent cases. 4) Integrating inter-professional practice requires optimizing the professional roles of other healthcare providers, and consequently redirecting patients to the appropriate provider to respond to patient’s needs in a timely manner. 5) Developing contingency plans facilitates planning for increased demand such as flu season, and proactive planning when providers are absent. Replacement coverage is organized either informally among counterparts or formally at the clinic level, to ensure that the capacity responds to patient demands at all times. Thus, implementing advanced access requires a major organizational change implying more broadly reorganizing the practice of the whole team members (administrative staff and health professionals) to be more patient-focused and efficient [9, 10].

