##### Measurement instruments

The *implementation of advanced access* will be assessed in both the organizational and provider surveys by measuring each of the five guiding principles of advanced access [35, 36] including their different sub-dimensions using a 5-point Likert scale. This section of the questionnaires is based on the work of: 1) VanDeusen et al. [10], who developed a questionnaire reflecting the operationalization of certain sub-dimensions of the guiding principles, as well as on a practice guide, *Advanced Access and Efficiency Workbook for Primary Care*, developed by *Health Quality Ontario* [37], which presents the operational definitions of the guiding principles of advanced access and 2) Orchard, King, Khalili et Bezzina [38] who designed and validated a short version questionnaire entitled *Assessment of Interprofessional Team Collaboration Scale*, particularly eight items on partnership. The *MIDI-Measurement Instrument for Determinants of Innovation*, developed by Fleuren et al. [31] will be used in both surveys to assess the *factors influencing the implementation of advanced access* in the UFMGs. The version of UFMG directors also includes an organizational survey based on the work of the Canadian Institute for Health Information [39], whose approval is already obtained. Some questions were, however, removed given that they were considered less relevant for this study or when the information was already available in the MHSS data bank. A pretest was done in the spring 2019 within a pilot project conducted in three UFMGs in one region (Estrie). Funded by the *Fondation Vitae*, this pilot project had enabled us to test the questionnaires in a real-world context and to improve them for the present study.

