##### Analysis

To respond to *objective 1* (assess the implementation of the five guiding principles of advanced access in the UFMGs), a score will be calculated for each principle, by type of respondent. Implementation scores will be assessed for each advanced access guiding principle by type of professional. Then, scores will be aggregated to produce group scores at the UFMG level for each of the above-mentioned principles. The median or average of all UFMGs’ score will be used as a threshold to determine the implementation categorization (e.g., strong/weak) of the advanced access for each principle. Descriptive analyses in terms of proportions, means, or standard deviations will be generated to determine the implementation scores of each principle and the factors influencing implementation. Multiple linear and logistic regression analyses will be performed using SAS 9.4 to determine the influence of different factors on implementation scores.

The Phase 1 results will be used to produce an implementation profile (e.g., strong/weak) of the UFMGs to guide the selection of the four cases which will be further analyzed in depth in Step 2.

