#### Step 2: Multiple contrasted case study based on mixed data

##### **A)** Qualitative component

***Data collection***

We will select four contrasted cases representing implementation profiles (*n* = 2 cases with high score, n = 2 cases with low score) and various geographical contexts and organizational size of UFMG (n = 2 cases in urban areas, n = 2 cases in rural/semi-rural areas). Previous studies have shown that context have a major influence on the types of collaborative practices among professionals [41].

For each UFMG in the study (*n* = 4), we will first perform a documentary analysis (e.g., algorithm of the patient’s path through advanced access, operating rules for team members). Then, a researcher and the research coordinator will conduct and record semi-structured interviews (60 min; at the UMFG) to reach data saturation (*n* = 11 interviews/case: two physicians, two PCNPs, two nurse clinicians, the physician in charge, one manager, two administrative assistants, one continuous quality improvement officer). The professionals will be recruited by email using purposive and snowball sampling strategies addressing first the medical director [42].

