*The average wait for the third available appointment.* This is the most accurate indicator for measuring the impact of advanced access implementation [37, 46]. It is used to assess the time required for an appointment and refers to the number of business days before the third available appointment in a professional’s schedule, for a regular or follow-up appointment [47]. It reflects availability more accurately than using the first or second available appointment, as these could result from a recent cancellation or an unanticipated event [13, 27]. As suggested by several authors, including the *Quality Improvement Guide* [48], Pickin et al. (2004) [27], and Jones et al. (2003) [49], we will calculate, every Tuesday, the median number of days until the third available appointment, and then the monthly average for each professional in the UFMGs [27].*Average rate of missed appointments (no-shows).* An underlying premises of advanced access is that providing a system of timely appointments leads to greater efficiency, with fewer missed (no-show) appointments [37]. Several studies have shown positive impacts on this indicator [50]. No-shows are defined as appointments that are scheduled but not used, excluding those cancelled or changed by the professional, and that are registered by the administrative staff in the EMR. We will calculate on a monthly basis, for each professional, the number of no-shows in relation to the total number of scheduled appointments [51]*.**Relational continuity.* Relational continuity is an important feature of primary care quality [48]. Patients followed by a professional whom they trust generate fewer visits [48]. While new organizational models rely on patients being managed by a team of professionals, advanced access aims first to optimize appointments with the professional to whom the patient is affiliated, depending on the need for the visit and the professional’s availability. Relational continuity is calculated as the number of visits with the physician and other team partner (e.g., nurses, residents) responsible for that patient’s follow-up care divided by the total number of that patient’s visits at the clinic [37*,*^48^]*. T*his indicator can be broken down into two complementary measures: 1) the number of visits the patient had with his/her affiliated physician divided by total number of visits to the UFMG; and 2) the number of visits with other team partner following that patient (e.g., nurses, residents) divided by the total number of visits to the UFMG. Relational continuity with the team will be obtained on a monthly basis for each patient from the sum of these two measures.*Organizational continuity measures*. The aim of advanced access is that patients will consult the primary care clinic to which they are affiliated to satisfy the majority of their needs. Organizational continuity measures the proportion of primary-care medical services patients receive at their UFMG where they are attached. This is measured by the number of consultations at the UFMG divided by the total number of primary care consultations (including visits both to the UFMG and to the emergency room for less urgent cases). Monthly measures of attendance rates of UFMG patients will be obtained from the MHSS, a partner in this study, which holds accurate measurement data of this indicator for all FMGs and UFMGs since January 2016.

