
***Analysis***

Descriptive analyses will be performed for all data, as well as graphic representations of the changes in monthly rates for each indicator aggregated to the level of each of the four selected UFMGs. Given the hierarchical nature of the data (repeated measures nested at the patient [indicator 3] or professional [indicators 1 and 2] level, which in turn are nested within the UFMGs), we will use multilevel analyses. These models will be adjusted to examine the effects of the various factors and of the implementation levels of advanced access on each of the three indicators. This type of model allows us to take into account the correlation between repeated measures for a single individual (patient or professional) over the study period, as well as missing data and patients lost to follow-up [52]. For the 4th indicator, trends will be analyzed using *join point* regression analyses [53]. This technique will be used to compare attendance rates among the 47 UFMGs and detect whether there have been significant changes in the direction or size of the linear trends for the rates over the 12 months of the study.

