## Discussion

This study addresses an important need identified by key stakeholders on timely access. In Canada, only 43% of the population report that they can see a doctor or nurse the same day or the next day when needed. This result is the lowest of all 11 Commonwealth Fund countries [56]. In recent years, advanced access has been widely implemented in primary care organizations as a promising solution to reduce wait times. Its implementation requires a major organizational change based on redesigning the work process of all the administrative staff and health professionals. However, despite its wide dissemination, we observe considerable variation in the implementation of the five guiding principles of this model not only among organizations, but also among professionals working within the same organization. Several scientific articles have studied the impacts of advanced access, and some have analyzed its implementation. Nevertheless, very few studies provide an in-depth understanding of the factors that explain the variations of the implementation levels and their impact on outcomes. This study will make a novel contribution to the field of implementation science and will fill an important gap in the literature on implementing advanced access in teaching primary healthcare clinics.

The findings will enhance understanding of how and why some primary care settings ensure successful implementation of advanced access and reduce wait times while others present a gap of implementation and fail to satisfy their patients’ needs and preferences with regards to timely access. More specifically, they will help to clarify which specific component (or guiding principle) of this complex innovation or which combination of guiding principles are critical to implementation effectiveness and should be prioritized by key stakeholders in particular contexts and by decisions makers to reduce wait times.

Identifying factors associated with successful implementation and positive outcomes provides useful lessons for future implementation and diffusion of advanced access in Quebec and across all Canadian provinces.

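### Principle 2 of the implementation score includes a result close to indicator 1 (wait), so their association may be partly built in

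*Protocol article*

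**What the plan says.** The Background (Importance and impact of the research) defines principle 2 as "Reducing the negative backlog by eliminating the wait list and setting up a communication strategy". Principle 3, in the same section, includes planning schedules so as "to permanently offer appointment slots (e.g. same-or next day) for acute and urgent cases".

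Under Step 1, Measurement instruments, each principle is measured by survey, "including their different sub-dimensions using a 5-point Likert scale". Under Step 1, Analysis, "scores will be aggregated to produce group scores at the UFMG level for each of the above-mentioned principles", and the median or average across clinics separates strong from weak implementation. Step 2, A) Qualitative component, takes four clinics, two with a high score and "n = 2 cases with low score", balanced also between urban and rural or semi-rural settings and varied in size.

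Under Step 2, B) Quantitative component, indicator 1 comes from the electronic medical record and "refers to the number of business days before the third available appointment" in a professional's schedule. Multilevel models then examine the effects of various factors and of the "implementation levels of advanced access on each of the three indicators". The Discussion says the findings will help clarify which principle or combination of principles "should be prioritized by key stakeholders in particular contexts and by decisions makers to reduce wait times".

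**The concern.** The Conceptual framework treats shorter waits as an impact of implementation, whereas the definition of principle 2 puts clearing the wait list inside implementation. A clinic with ample staffing or light demand may have no wait list whatever it did about advanced access. If staff rate that state, the clinic scores higher on principle 2 and will also tend to show a short wait for the third available appointment.

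Part of the contrast in wait between high and low cases could then appear even if none of the five principles had any effect. The Discussion makes this matter: it intends to advise decision-makers on which component to prioritise for wait times, and principle 2 would enter that comparison with an advantage. The article does not mention the overlap and plans no wait analysis that leaves this content out.

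**Working it through.** The article states no figure to reproduce, because the point concerns the overlap of two constructs. The sizes below rest on labelled assumptions.

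**Inputs from the article:** five principles; 47 clinics scored; four clinics (two high, two low) with wait data. **Not in the article:** the item wording, any composite across principles, and the correlation of backlog with wait.

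**1. Built-in correlation of principle 2 with wait.** Let *w* be the share of principle 2 score variance that reflects backlog state, and *r* the correlation of backlog state with wait. If no principle has any effect, the correlation is -*r*√*w*.

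| *w* | *r* = 0.3 | *r* = 0.6 | *r* = 0.9 |
|---|---|---|---|
| 0 | 0 | 0 | 0 |
| 0.25 | -0.15 | -0.30 | -0.45 |
| 0.5 | -0.21 | -0.42 | -0.64 |
| 1 | -0.30 | -0.60 | -0.90 |

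**2. Carry-over to a composite.** Assume an equal-weight average of five standardised scores, a common inter-principle correlation ρ, and only principle 2 related to wait, with correlation *c*. The average then correlates *c*/√(5(1+4ρ)) with wait. For *c* = -0.6:
- ρ = 0: -0.6/√5 = -0.27
- ρ = 0.3: -0.6/√11 = -0.18

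**3. Score contrast between high and low cases.**
- Strict extremes, the top two and bottom two of 47 normal scores: the mean of the top two is 2.03, so the contrast is 2 × 2.03 = 4.06 SD.
- Random picks within each half of a median split: about 1.6 SD.

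**4. Built-in difference in wait** (correlation × contrast, in SD of clinic wait).

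| Case selection | ρ = 0 | ρ = 0.3 |
|---|---|---|
| Random within halves | 0.27 × 1.6 = 0.43 | 0.18 × 1.6 = 0.29 |
| Strict extremes | 0.27 × 4.06 = 1.10 | 0.18 × 4.06 = 0.73 |

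The range is about 0.3 to 1.1 SD. It scales directly with *c*, so *c* = -0.3 would halve it. The value -0.6 lies toward the strong end of the *w* = 0.25 to 0.5 rows in step 1.

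**5. Would principle 2 come out first?** Simulation with no true effect of any principle, the other four independent of wait, and four clinics drawn at random (20,000 runs): the share of runs in which principle 2 has the most negative correlation with wait was
- *w* = 0: 20%, which is chance
- *w* = 0.25: 25% to 40% over *r* = 0.3 to 0.9
- *w* = 0.5: 28% to 52%
- *w* = 1: 31% to 79%

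With 47 clinics (5,000 runs) the shares would be 50% to 96% at *w* = 0.25 and 64% to 100% at *w* = 0.5, but the plan collects this wait in four clinics only.

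**The case against.** The strongest reply is that the definition describes the advanced access model, not the questionnaire. The items are not shown, which is normal for an article, and they may record actions such as a backlog plan or letters to patients. In that case the built-in part is zero. This stands, and it makes the point conditional.

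A reader might infer that principle 2 is indicator 1 under another name, so that the link is true by definition. The article does not support that. One is a staff survey score that also covers communication with patients; the other is a count of business days read from the medical record. They are related, not identical. A separate source does not remove the overlap, however, if staff are rating the same underlying state.

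A reader might also infer that principle 2 is bound to rank first. It is not: with four clinics at moderate overlap it does so in about 25% to 52% of simulated studies, against 20% by chance. The Analysis section specifies no ranking, and the Discussion sentence is a broad aim of the whole mixed-methods study.

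The article states neither an equal-weight composite nor selection of strict extremes, and balancing setting and size pulls selection away from the extremes. That is why the range starts at the random-within-halves contrast.

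With two clinics against two, the standard error of a clinic-level difference is √(1/2 + 1/2) = 1 SD of clinic means, so a built-in difference of this size could pass as chance. That means it may go unnoticed, not that it is absent.

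Finally, backlog reduction belongs to the model under study, and an association with wait could be its real effect. This argues against removing it from case selection, but not against showing how far the result depends on it.

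**Conclusion.** The concern holds conditionally. As defined, principle 2 contains a result-type element close to indicator 1, and the plan uses implementation level to explain that indicator without separating the two. To the extent that items rate the state reached, the association with wait is partly built in and the reading of which principle to prioritise is tilted toward principle 2.

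The size cannot be derived from the article. It runs from zero (items on actions only) to about 0.3 to 1.1 SD of clinic wait under the assumptions set out above: principle 2–wait correlation -0.6, the other principles unrelated to wait, inter-principle correlation 0 to 0.3, an equal-weight composite, and selection between random within halves and strict extremes.

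The access content of principle 3 deserves the same check. No-shows, relational continuity and organizational continuity are not touched. This is an inexpensive improvement to the indicator 1 analysis. It does not invalidate the design or require the cases to be chosen on a different score.

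**What to change.** - Before the analysis, mark which principle 2 items rate backlog or wait-list status and which rate actions. Do the same for items on same- or next-day availability in principle 3.
- For indicator 1, report the analysis with the full five-principle score and again with a score that leaves out the status items. If there are no such items, say so; the point then falls away.
- Report the status items alongside the outcomes.
- Check whether the four cases keep their high or low standing under the reduced score, and state the result.
- Do not rank principles on wait from four clinics, and word the Discussion aim accordingly.

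The cost is one alternative score from items already collected and one repeated analysis. The reduced score no longer covers all of principle 2, which is why both versions are shown. The full score stays in use for the Phase 1 description and for the other indicators.
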